### tDCS intervention

Home-based tDCS will be delivered via a Soterix 1 × 1 mini-CT remote tDCS neuromodulation device (Soterix, New York, NY). The device will be equipped with a two-channel Omni-Lateral-Electrode-System (OLE) montage. The OLE montage is specific to left DLPFC targeting, delivering anodal stimulation to the left DLPFC and cathodal stimulation to the right DLPFC [31]. In the standard view of tDCS, anodal stimulation results in an excitatory response in the underlying brain region, and cathodal stimulation results in an inhibitory response [32]. Given that the left DLPFC is typically underactive in children with ASD, anodal stimulation over this area might increase the opportunity for activity to increase to typical levels. Anodal stimulation over left DLPFC has been shown to improve executive functioning in individuals with autism [33–35]. The results of stimulation of the right DLPFC have been mixed, with both anodal and cathodal stimulation showing positive effects on behavior [36]. Neuroimaging studies have also shown both hypo- and hyperactivation in the right DLPFC of children with autism when compared to controls. These findings indicate that modulation of both the left and right DLPFC may contribute to improvements in behavior. The left anodal and right cathodal montage have shown the most promising results in tDCS studies in this population and is the most well-documented [18, 36–40].

Participants in the active tDCS group will receive a total of 20 min of stimulation per session, at a maximum of 2 mA intensity. For the sham tDCS control group, the same device, montage, and protocol will be used, but the device will be programmed for the sham condition. This condition delivers 30 s of stimulation (max. 1.0 mA) at the start and end of the session to mimic the sensation of the active condition. This is the proven gold standard for participant blinding and sham-control [41–43]. The first treatment session will ramp up to 1.0 mA for all participants. Participants in the sham tDCS group who tolerate 1.0 mA will remain at 1.0 mA in each treatment session. Participants who do not tolerate 1.0 mA will have the current adjusted to 0.75 mA and 1.0 mA will be attempted again at the next session. For the active tDCS group, if 1.0 mA in the first treatment session is tolerated, the second treatment session will begin at 1.5 mA. If 1.0 mA is not tolerated, the session will start at 1.0 mA. If 1.5 mA is tolerated throughout the second treatment session, the third treatment session will begin at 2.0 mA. If 1.0 mA is tolerated throughout the second treatment session, the third treatment session will begin at 1.5 mA. For the remainder of sessions, the intensity tolerated in the final 10 min of one treatment session will serve as the starting point in the next treatment session. If a participant is not tolerating a certain intensity at any point during treatment, it will be reduced by 0.25–0.5 mA, and their symptoms will be re-evaluated at the reduced intensity and adjusted accordingly.

A summary of the study schedule is shown in Fig. 1. All in-person assessments will be conducted at Holland Bloorview Kids Rehabilitation Hospital in Toronto, Canada. The take-home tDCS device will be provided at the first baseline assessment visit (T0). The participant and/or caregiver will be trained on administration and device use by a study team member. The study team member will demonstrate how to use the device on the participant in a step-by-step manner. Following the demonstration, the caregiver or participant will attempt to recreate the demonstration, and the study team member will observe to ensure they are following the steps correctly and assist with any questions or concerns. The following week, participants will begin home-based tDCS treatment sessions. Fifteen sessions will be conducted over 3 weeks (5 days/week, Monday–Friday), with remote support from the study team via videoconferencing [42, 44]. Each session will be 30 min in duration, including a 5-min intake and equipment set-up, 20-min tDCS, and 5-min debrief and observation to ensure there are no unanticipated adverse events [34, 45]. Previous studies have shown that 15 sessions of 20-min tDCS at 2 mA may be effective in this population for a variety of behaviors [18, 46].

**Fig. 1 Fig1:**
[figure not shown]
Overview of the study design. (*) designates portions that can be completed virtually

### Primary outcome measures

The primary objectives of this study are to assess the feasibility, tolerability, and acceptability of an RCT to test the efficacy of tDCS. Feasibility measures are based on a hypothetical sample size of 100 participants for a full-scale RCT, based on previous neurostimulation clinical trials [47–51].

#### Feasibility

Feasibility measures include recruitment rate, retention rate, adherence rate, and success of randomization and blinding. Recruitment and attrition will be calculated using the electronic audit trail generated by the documentation kept by the independent RA and statistician and research assistant. Adherence will be calculated based on the number of sessions attended and completed by participants who complete all assessments. The success of blinding will be determined based on responses to the questions “What group do you think you were in?” and “How sure are you?”, which will be asked on the follow-up tolerability questionnaire (adapted from Garvey et al., 2001) [52]. Descriptive statistics will be completed to establish if the comparison and intervention groups are similar in age, gender, ASD severity, and clinical symptom severity. The success of randomization will be determined by evaluating group differences in sex distribution and median age. Randomization will be determined to be successful if the differences in sex distribution are within ± 2 participants, and the median age difference is within ± 2 years.

The feasibility of the optional MRI component will be evaluated based on total and successful attempts at completing the MRI protocol. There is a paucity of data on neural outcomes in this population; therefore, any amount of data collected is valuable. Previous MRI studies examining children with ASD include samples between 20 and 50 participants [53–57]. In a hypothetical sample size, *n* = 100 (*n* = 50 per group) for a full-scale RCT, including data from at least 20 individuals in each group would be sufficient to conduct an analysis. Given this, the optional MRI component of this study will be feasible if ≥ 20% of participants in each group have successful MRIs. A successful attempt is one in which a majority of the scan is completed with minimal motion artifact as determined by the MRI technician.

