### Data analysis

#### Primary measures analysis

##### Feasibility

Feasibility measures will be analyzed as per the progression criteria outlined in Table 1. These criteria were determined based on recommendations by Avery et al. to assess whether to proceed with a full-scale RCT [75]. Associations between participant characteristics (e.g., age, IQ, travel distance) and ability to complete all trial tasks will be examined to inform the planning of a large-scale RCT. *T*-tests will be conducted for associations with continuous variables (e.g., IQ, age, travel distance). Chi-squared tests will be conducted for associations with categorical variables (e.g., gender).

**Table 1 Tab1:** Progression criteria for feasibility metrics

	**GO–proceed with RCT**	**AMEND–proceed with changes**	**STOP–do not proceed unless changes are possible**
Recruitment target	*n* = 46	*n* = 36–45	*n* < 36
Adherence	≥ 90% of tDCS sessions are completed by participants who complete all assessments	70–89% of tDCS sessions are completed by participants who complete all assessments	< 70% of tDCS sessions are completed by participants who complete all assessments
Participant retention	≥ 90% retention	80–89% retention	< 80% retention
Optional MRI target	≥ 20% of participants have successful MRIs in each group	10–19% of participants have successful MRIs in each group	< 10% of participants have successful MRIs in each group

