##### Safety and tolerability

Safety will be assessed by the occurrence of side effects as reported on the systems and NIBS tolerability questionnaires, in addition to the instances and severity of AEs. A correlational analysis will be conducted between the occurrence of side effects and feasibility measures to assess the association between these factors.

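### Adherence is calculated only in children who complete every assessment, so Table 1 can read GO when adherence among all randomised children is in the AMEND range

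*Protocol article*

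**What the plan says.** The Feasibility paragraph under Primary outcome measures fixes the analysis set: "Adherence will be calculated based on the number of sessions attended and completed by participants who complete all assessments". All three adherence cells of Table 1 repeat the restriction:

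- GO: "≥ 90% of tDCS sessions are completed by participants who complete all assessments"
- AMEND: "70–89% of tDCS sessions are completed by participants who complete all assessments"
- STOP: "< 70% of tDCS sessions are completed by participants who complete all assessments"

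The wording is consistent and looks deliberate. No adherence figure over all randomised participants is given.

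Loss of participants is scored in a separate row of the same table: GO at "≥ 90% retention", AMEND at "80–89% retention", STOP below 80%. The article does not say who counts as retained.

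Under Data analysis, Safety and tolerability, the feasibility measures are used again: "A correlational analysis will be conducted between the occurrence of side effects and feasibility measures".

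**The concern.** Whether a child enters the adherence rate depends on something that happens after randomisation: completing every assessment up to T2, which the Design section puts 12 weeks after a 3-week treatment course. A child who finds the daily sessions too burdensome, stops and leaves the study disappears from the measure meant to detect that. A child with 15 of 15 sessions who misses T2 also disappears, although the Secondary measures analysis section would admit that child to the secondary analyses (baseline plus at least one follow-up). The primary criterion therefore rests on a narrower set than the secondary ones.

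Whether families can sustain 15 sessions at home is a central question of a home-based pilot, and the answer feeds a decision on a full-scale trial. Where completers attended more sessions than the others, the row gives too favourable an answer. It may also point the remedy at follow-up when the difficulty lies in the sessions. In the side-effect correlation, the adherence value is missing for children who quit early, who are informative about that link.

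**Working it through.** **Inputs from the protocol.** 46 participants (Sample size); 15 sessions each (tDCS intervention), so 46 × 15 = 690 scheduled sessions; adherence bands at 90% and 70% and retention bands at 90% and 80% (Table 1).

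**Assumptions.** The sessions done by each non-completer, s, are not in the protocol; 0, 3, 7.5 and 15 are shown. Retained is first taken to mean completing all assessments.

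**Formula.** With c completers whose adherence is a:

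adherence over all randomised = (c × 15 × a + (46 − c) × s) / 690

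**Step 1: the smallest c for which retention reads GO.** 42/46 = 91.3% (GO); 41/46 = 89.1% (AMEND). So c = 42 is the least favourable case in which retention raises no flag.

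**Step 2: c = 42, a = 90%.** Completers do 42 × 15 × 0.90 = 567 of 630 sessions, so the adherence row as written reads GO. Over all 46:

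| Sessions by each of the other 4 | Calculation | Adherence, all randomised | Band |
|---|---|---|---|
| 0 | 567/690 | 82.2% | AMEND |
| 3 | (567 + 12)/690 | 83.9% | AMEND |
| 7.5 | (567 + 30)/690 | 86.5% | AMEND |
| 15 | (567 + 60)/690 | 90.9% | GO |

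**Step 3: how high completer adherence must be for both figures to read GO.** 90% of 690 is 621 sessions. With s = 3 the completers must supply 621 − 12 = 609 of 630, or 96.7%. At 97% the result is (42 × 15 × 0.97 + 12)/690 = 90.3%, GO. So with s = 3, completer rates from 90% to just under 96.7% give GO as written and AMEND over all randomised.

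**Step 4: can the gap reach STOP?** Take the worst case, a = 90% and s = 0:

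- c = 37: 37 × 0.90/46 = 72.4% (AMEND); retention 37/46 = 80.4% (AMEND)
- c = 36: 36 × 0.90/46 = 70.4% (AMEND); retention 36/46 = 78.3% (STOP)
- c = 35: 35 × 0.90/46 = 68.5% (STOP); retention 35/46 = 76.1% (STOP)

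The adherence row can read GO with all-randomised adherence below 70% only if 35 or fewer complete, and retention is then itself STOP.

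**Step 5: if retained is read more loosely.** Suppose 38 complete everything at 90%, four more miss one assessment but count as retained, and four leave. Retention is 42/46 = 91.3% (GO) and adherence as written is 90% (GO). If the eight non-completers did 3 sessions each, adherence over all 46 is (38 × 15 × 0.90 + 24)/690 = 537/690 = 77.8%. The same two GO readings now cover a larger shortfall.

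**The case against.** The strongest reply is that the table already scores children who leave, in its own row. Keeping apart who stayed and how much treatment the stayers received is a coherent choice, and an all-randomised rate counts each early withdrawal twice. Much of this stands. If retained means completing all assessments, then at 41 or fewer completers the retention row is at least as severe as all-randomised adherence would be (given completer adherence of 90% or more). A reader might infer that the plan can wave through a regimen whose true adherence is in the STOP range. On that reading the protocol does not support this, because retention would read STOP as well.

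It is also fair that upward bias is not automatic. The protocol's expected 10% is loss to follow-up, not early withdrawal from treatment. A child lost between T1 and T2 may have done all 15 sessions, and leaving that child out does not inflate the rate. With 41 completers at 92% and five others at 12 sessions each, the figure is (565.8 + 60)/690 = 90.7%, still GO.

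Nor is the side-effect correlation lost altogether. Side effects are recorded at every session and retention is also a feasibility measure, so early quitters still contribute there. Only the adherence part omits them.

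Two things remain. With 42 to 45 completers both rows can read GO while adherence over all randomised is AMEND. And the retention guard depends on a definition that the article does not give.

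**Conclusion.** The concern holds in a limited form. The completers-only denominator can turn an AMEND into a GO with no other row flagging it, at drop-out close to what the protocol expects: 42 of 46 completing at 90% adherence corresponds to 82.2% to 86.5% over all randomised if the other four did none to half of their sessions. The overstatement at that point is at most 90 − 82.2 = 7.8 percentage points. It does not move the band if the four did all 15 sessions, or if completers reach about 97% with 3 sessions from each of the others.

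This rests on an assumed number of sessions among non-completers, on taking retained to mean completing all assessments, and on the least favourable row governing the decision, which the article does not state. If a child who misses one assessment can count as retained, the shortfall behind two GO readings can be larger.

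**What to change.** - Define adherence as sessions completed divided by 15 scheduled for every randomised participant, with sessions missed after withdrawal counted as not completed. Report it overall and by arm.
- Apply the 90% and 70% bands in Table 1 to that figure, and keep the completers-only rate as a descriptive result.
- State in Table 1 that retained means completing all assessments.
- Use the all-randomised value in the adherence part of the side-effect correlation.

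The cost is a reworded definition and changes to two table rows. No new data are needed: every session is supported by videoconference and has its own questionnaires, so attendance is known whether or not T1 and T2 are completed. The reported rate will probably be somewhat lower, and an early withdrawal will count in both the adherence and the retention rows. The report should say so.

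### The MRI GO threshold of 20% per group does not follow from the protocol's own figures: 20 of 50 per group is 40%, and 20% projects to 10 scans per group

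*Protocol article*

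**What the plan says.** The opening of Primary outcome measures in the protocol article gives the planning basis: "Feasibility measures are based on a hypothetical sample size of 100 participants for a full-scale RCT". The Feasibility section below it divides that total into 50 per group. It then states that "including data from at least 20 individuals in each group would be sufficient to conduct an analysis", and draws the criterion directly from that statement: "the optional MRI component of this study will be feasible if ≥ 20% of participants in each group have successful MRIs".

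Table 1 (progression criteria, under Data analysis) carries the figure into the decision rule. GO for the optional MRI target is "≥ 20% of participants have successful MRIs in each group", AMEND is 10–19%, and STOP is below 10%.

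**The concern.** The target count, the group size and the threshold are all expressed per group, and the text presents the third as following from the first two. It does not: the printed percentage is half of what the two inputs give.

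The MRI row is one of four in the progression table, so the figure will be used to make a decision. As printed, the pilot can return GO for the MRI component when its own success rate, carried to the full trial, would deliver only half the scans that the protocol names as enough for an analysis. A team relying on the table could then budget scanner time and plan imaging outcomes for a trial that is unlikely to reach that number.

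**Working it through.** **Inputs from the protocol article**
- Full-scale trial: 100 participants, 50 per group (Primary outcome measures; Feasibility).
- Number of MRI datasets described as sufficient: at least 20 per group (Feasibility).
- GO threshold: 20% or more in each group (Feasibility; Table 1). AMEND: 10–19% (Table 1).
- Pilot: n = 46 allocated 1:1, so 46/2 = 23 per group (Sample size; Randomization and blinding).

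**Can the printed 20% be reproduced?**
- Per-group count over per-group size: 20/50 = 40%.
- Both groups over the total: 40/100 = 40%.
- Per-group count over the total: 20/100 = 20%. This gives the printed number, but it mixes a per-group numerator with a whole-trial denominator.
- 20 scans in the whole trial over the total: 20/100 = 20%. This also gives the printed number, but it conflicts with the statement that the 20 are in each group.

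So 20% arises only if one of the stated inputs is read differently from how it is written.

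**What the printed bands project to in the full trial**
- GO at exactly 20%: 0.20 × 50 = 10 scans per group, 20 in total, against 20 per group and 40 in total.
- AMEND: 0.10 × 50 = 5 to 0.19 × 50 = 9.5 per group.
- Group size at which 20% would give 20 scans: 20/0.20 = 100 per group, a trial of 200.

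**What the rule asks of the pilot (23 per group)**
- 20%: 0.20 × 23 = 4.6, so 5 scans per group.
- 40%: 0.40 × 23 = 9.2, so 10 scans per group.

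**How the two thresholds behave**

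The true success rate p is an assumption, because the protocol gives none. It is taken as equal in the two groups, participants are treated as independent, and all 23 per group are in the denominator. With exact binomial tails:
- P(GO at 20%) = P(X ≥ 5 | 23, p)²
- P(GO at 40%) = P(X ≥ 10 | 23, p)²
- P(full trial reaches 20 in both groups) = P(X ≥ 20 | 50, p)²

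| True rate p | P(GO), 20% threshold | P(GO), 40% threshold | P(at least 20 of 50 in both groups) |
|---|---|---|---|
| 20% | 0.249 | 0.0001 | <0.0001 |
| 30% | 0.864² = 0.747 | 0.120² = 0.014 | 0.0848² = 0.007 |
| 40% | 0.962 | 0.444² = 0.197 | 0.554² = 0.306 |
| 45% | 0.989 | 0.636² = 0.405 | 0.803² = 0.644 |

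At a true rate of 30% the printed rule says GO about three times in four, although the full trial would then expect 0.30 × 50 = 15 scans per group and would almost never reach 20 in both.

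**The case against.** The strongest reply is that the protocol does not treat 20 per group as a minimum. It calls that number sufficient, and the same paragraph says that, with so little neural data in this population, any amount is valuable. A reader might infer from the arithmetic that 10 scans per group would be too few to analyse. The text does not say so. That part of the reply stands, and the claim here is only that 20% does not deliver the number called sufficient. The reply does not rescue the threshold, because the protocol derives it from the 20-per-group figure and not from the general value of any data.

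A second reply is that the percentage may be right and the target wrong. The earlier MRI studies cited had between 20 and 50 participants, and the text does not say that these are per-group counts. If 20 scans in total was meant, 20% of 100 is correct and the slip lies in assigning 20 to each group. The document does not settle which figure is wrong, so the error cannot be attributed to the percentage with certainty.

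Table 1 taken alone might also be stretched to mean 20% of all participants, found within each group. The Feasibility sentence, which refers to "20% of participants in each group have successful MRIs", does not allow that reading.

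The definition of success ("A successful attempt is one in which a majority of the scan is completed with minimal motion artifact") could tempt a reader to infer that a baseline-only scan, or one missing a sequence, counts towards the target. The article is silent on visit and sequence, such detail is commonly left to the full protocol or analysis plan, and baseline imaging has a planned use of its own in the Neural analysis section. No finding is made on that.

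Finally, the MRI is optional and serves a secondary objective. That limits the consequence but does not remove the inconsistency.

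**Conclusion.** The point holds as an internal contradiction. The stated inputs give 40% per group; the Feasibility section and Table 1 both print 20%, and nothing elsewhere in the article repairs it. The printed GO level projects to 10 scans per group where the protocol calls 20 sufficient, and in the pilot it sets the requirement at 5 scans per group where 40% would set it at 10.

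The arithmetic needs no assumption beyond the protocol's own figures. The probabilities (about 75% for GO against about 0.7% for reaching 20 scans in both groups) rest on an assumed true success rate of 30%, equal in both groups, with 23 per group in the pilot and 50 per group in the full trial.

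A reader might take the point to mean that the pilot could wrongly send the whole trial forward. It does not go that far: this row governs the optional MRI component, and the recruitment, adherence and retention rows are unaffected.

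**What to change.** Reconcile the Feasibility sentence with the MRI row of Table 1 before the criterion is applied. There are two consistent routes:

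1. If 20 per group is the intended target, set GO at 40% or more in each group and reset the AMEND and STOP bands to match.
2. If 20 scans in total was intended, keep 20%, restate the target as about 10 per group, and justify that number.

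Either route changes one sentence, one table row, or both.

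The cost of the first route is strictness. With 23 per group, a 40% threshold applied to both groups gives GO only about 20% of the time when the true rate is exactly 40%, and about 40% of the time when it is 45%. Much of the decision would then fall to AMEND, so the lower limit of that band should be chosen with this in mind and not simply doubled by default. The cost of the second route is that the protocol must defend a smaller imaging sample than the one it now calls sufficient.

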### Sample size

Pilot RCTs do not test efficacy, and formal sample size calculations are not typically used. However, if too small, a pilot study may underestimate the standard deviation leading to underpowered efficacy RCTs. Sim et al. [30] suggested that the sample size of a pilot study be determined based on the desired level of confidence for the standard deviation of the primary outcome measure in the larger-scale RCT, and the power and significance level anticipated. Additionally, attempts to minimize the total sample size required should be made. Given an expected 10% loss to follow-up, and to maintain equal group sizes, the proposed pilot sample size will be *n* = 46. This is adequate to assess recruitment success and feasibility issues and provides sufficient data for exploratory analysis of the secondary outcomes.

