#### Neural

At the baseline assessment (T0), participants will undergo optional high-resolution MRI on a Siemens 3 T Prisma MRI. Structural T1-MPRAGE, DTI, and resting-state functional MRI data will be collected at all time points (T0–T2). Acquisition of neuroimaging data will allow for the investigation of changes at immediate post-treatment (T1) and maintenance at long-term follow-up (T2).

At the baseline assessment, participants will undergo an optional high-resolution MRI on a Siemens 3 T Prisma MRI. Structural (T1 and diffusion tensor imaging) and resting-state functional MRI data will be collected at all timepoints. Acquisition of neuroimaging data will allow for the investigation of changes at immediate post-treatment and maintenance at long-term follow-up.

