##### Neural

Structural and functional neuroimaging changes between timepoints T0, T1, and T2 will be compared between groups, and associations between baseline neuroimaging and treatment outcomes will be explored. Freesurfer (https://surfer.nmr.mgh.harvard.edu/) will be used to obtain cortical thickness from structural MRI data. MRtrix3 software will be used to process diffusion imaging data to determine changes in white matter tracts [76]. Blood-oxygen-level-dependent (BOLD) signal of resting-state functional MRI will be analyzed using the fMRIPrep pipeline. All results will be corrected for multiple comparisons using the false discovery rate (FDR) method (*P*_FDR_ < 0.05). Changes in network activity will be analyzed using the left DLPFC as a seed.

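### The MRI progression criterion does not say which visits or sequences must succeed, so GO can be met without the paired scans the neural comparison needs

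*Protocol article*

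**What the plan says.** In the protocol article, Primary outcome measures, Feasibility, the optional MRI is assessed by attempts: "The feasibility of the optional MRI component will be evaluated based on total and successful attempts at completing the MRI protocol". Success is defined at the same level: "A successful attempt is one in which a majority of the scan is completed with minimal motion artifact as determined by the MRI technician". The reason given for having a threshold is analytic. For a full trial with 50 per group, "including data from at least 20 individuals in each group would be sufficient to conduct an analysis".

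Table 1 (Data analysis, Feasibility) turns this into a progression rule, with GO if "≥ 20% of participants have successful MRIs in each group", AMEND at 10–19% and STOP below 10%. Neither place names a visit, a number of visits or a sequence.

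The imaging plan is serial and has three parts. Secondary outcome measures, Neural, schedules T1-MPRAGE, DTI and resting-state fMRI at T0, T1 and T2. Under Secondary measures analysis, Neural: "Structural and functional neuroimaging changes between timepoints T0, T1, and T2 will be compared between groups". The same sentence adds an exploratory look at baseline imaging against treatment outcome. The opening of Secondary measures analysis limits the analyses to participants with baseline data and at least one follow-up.

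**The concern.** The unit that is scored (an attempt, mostly completed) differs from the unit that is analysed (a child with a before-and-after pair in a given modality). A child with one good scan can count towards GO but gives nothing to the between-group comparison of change. Applied to the imaging outcomes, the rule of baseline plus follow-up leaves that child out. A session in which the structural and diffusion sequences were completed but the resting-state run was lost can pass as a majority and still give no functional outcome.

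The MRI row feeds a decision on whether imaging belongs in the full RCT. A GO reached through single or partial scans would be read as support for serial three-modality MRI, although the pilot had not shown that such data can be obtained.

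**Working it through.** **Inputs from the protocol article.** Pilot size: "the proposed pilot sample size will be *n* = 46" (Sample size). Allocation 1:1 (Randomization and blinding). GO threshold 20% per group (Table 1). Planning case: "In a hypothetical sample size, *n* = 100 (*n* = 50 per group) for a full-scale RCT", with 20 per group called sufficient (Feasibility). The document gives no success rate by visit or by sequence.

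**1. The plan's own figure.** 20 / 50 = 40%, so the stated 20% is not reproduced. It appears only if 20 is divided by the total of both groups (20 / 100). Conversely, 20% of 50 is 10 children per group. This is a separate point, noted here because it limits what a better definition of success can achieve.

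**2. Children needed for GO in the pilot.** 46 / 2 = 23 per arm, and 0.20 × 23 = 4.6, so 5 per arm. With 21 per arm after losses, 0.20 × 21 = 4.2, again 5.

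**3. What GO guarantees as written.** Five children per arm with one successful scan each satisfy the wording, and the number of T0-to-follow-up pairs is then 0. This step needs no assumed rate.

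**4. Sequences.** Two of three sequences is 2 / 3 = 67% of the scan if they are equally long (an assumption, since durations are not given). That is a majority with one modality absent.

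**5. Illustration with conditional repeat success.** Let *a* be the share of an arm with a successful T0 scan, and *b* the probability of success at each later visit given success at the one before (both assumed). Pair T0–T1 = *a* × *b*; all three visits = *a* × *b*².

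| *a* | *b* | T0–T1 pair | children of 23 | all three visits |
|---|---|---|---|---|
| 0.30 | 0.60 | 0.180 | 4.1 | 0.108 |
| 0.30 | 0.80 | 0.240 | 5.5 | 0.192 |
| 0.40 | 0.60 | 0.240 | 5.5 | 0.144 |
| 0.40 | 0.80 | 0.320 | 7.4 | 0.256 |

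All four rows are GO if the T0 scan alone is counted. By T0–T1 pair, only the first row falls below 20%. A child who misses T1 but is scanned at T2 also has a usable pair, so the share with T0 plus any follow-up is at least the pair column.

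**6. A harsher illustration.** Assume success probability *s* at each of three visits, independent within a child, with any one success counting. Any success = 1 − (1 − *s*)³. T0 plus a follow-up = *s* × [1 − (1 − *s*)²]. P(GO in both arms) = P(Binomial(23, *p*) ≥ 5)², where *p* is the share concerned.

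| *s* | any scan | T0 + follow-up | P(GO), any scan | P(GO), T0 + follow-up |
|---|---|---|---|---|
| 0.3 | 0.657 | 0.153 | 1.000 | 0.073 |
| 0.4 | 0.784 | 0.256 | 1.000 | 0.545 |
| 0.5 | 0.875 | 0.375 | 1.000 | 0.935 |

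Independence probably exaggerates the gap, since a child who tolerates one scan is likelier to tolerate the next.

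**The case against.** The strongest reply is that the protocol nowhere says one attempt is enough. Table 1 speaks of MRIs in the plural, and completing the MRI protocol could mean completing the series. A reader might infer that single-scan counting is the stated rule. The text does not support that: the number of visits is left open. The plural may equally be the ordinary one for several participants, and the only definition supplied is per attempt. What stands is that the rule permits single-scan counting, not that it prescribes it.

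A reader might also infer that a child scanned only at T0 is of no use. That is wrong as well. The exploratory associations with baseline imaging need only T0, and the authors regard any imaging data in this population as worth having. But they base the criterion on an analysable number per group, and the between-group comparison is of change.

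The analysis itself is not corrupted, because the requirement of baseline plus follow-up removes unpaired children there. They stay in the GO count, however. The retention row in Table 1 limits loss through dropout but not refusal or failure of a repeat scan. Total attempts will also be looked at, although no band is attached to them.

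An article may leave visit counting and quality-control cut-offs to the full protocol. Here, though, a definition of success is given, and it does not match the purpose stated beside it. Finally, MRI is optional in this pilot, which limits the weight of the point.

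**Conclusion.** The point holds as a mismatch between a stated decision rule and its stated purpose. The certain part is that the 5 of 23 per arm needed for GO can be made up of children with no before-and-after pair, or of scans missing a modality.

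How far GO would mislead in practice cannot be read from the document. Under the assumed rates, three of the four T0–T1 pair results stay at GO. The two ways of counting differ most when scanning is difficult. It would go too far to say that the pilot will hold too few paired scans, or that GO will be wrong. It would also go too far to expect that redefining success secures 20 per group: at the 20% threshold, a trial with 50 per group has 10 qualifying children per group, however success is defined. This is a worthwhile and cheap correction to one optional component.

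**What to change.** For the MRI row of Table 1, count a participant as successful only with usable T0 data plus at least one usable follow-up scan, in line with the rule already set for secondary analyses. Requiring T1 specifically would fail children with T0 and T2 scans whom that rule accepts. Make the count separately for T1-MPRAGE, DTI and resting-state fMRI, and confirm usability after processing with the pipelines named under Secondary measures analysis, Neural, in addition to the technician's judgement at the scanner. State the quality-control standard beforehand. Report single-visit success and T0–T1–T2 completeness alongside.

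The cost is rewording the definition and the table row, preferably before results are seen. No extra scans are needed, and the reported MRI success rate becomes less favourable. The threshold itself (20% against 20 of 50) should be settled separately.
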